#### Statistical analysis

An intention-to-threat analysis will be used to preserve the effects of group allocation and provide an assessment of the practical impact of the treatment [74], as recommended by the CONSORT statement [75]. The normality of continuous outcomes will be assessed via the Kolmogorov-Smirnov test. Comparisons of the initial and final data will be analyzed via a two-way repeated-measures analysis of variance, and the categorical outcomes, via the *χ*^2^ test. A partial correlation will be used to test the effects of airway and systemic inflammation as mediators. P values ≤ 0.05 will be considered statistically significant. The statistical analysis will be blinded to the treatment allocation and will be performed using specific software (SigmaStat 3.5, Systat Software Inc.).

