### Experimental design

The patients will be assessed before and after the interventions on 3 non-consecutive days. On day 1, anthropometric indexes, body composition, asthma symptoms and peripheral muscle strength will be assessed. On day 2, asthma clinical control will be assessed via an asthma control questionnaire (ACQ), an asthma quality of life questionnaire (AQLQ), and a hospital anxiety depression scale (HADS); sleep disorder history, lung function and exercise capacity will be also assessed. On day 3, the exhaled fraction of nitric oxide (FeNO), daily life physical activity and systemic inflammation will be measured. Following these baseline evaluations, all eligible patients will receive a 6-h educational program and will be subsequently randomly assigned into the following 2 groups: either a weight loss program (including nutritional and psychological therapy) with a sham treatment (WL + S group), or the same weight loss program with exercise (WL + E group). All patients will complete 24 treatment sessions, after which they will be reevaluated.

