### Outcomes

#### Primary outcome

The primary outcome of this study will be the absolute change in the asthma control questionnaire (ACQ) post intervention between the groups following the intervention. The ACQ is both a reliable and validated method of measuring the impairment in asthma control [44, 45] and includes specific parameters regarding both daytime and nocturnal asthma symptoms, activity limitations, dyspnea, wheezing and rescue bronchodilator use within the last week (a short-acting B_2_-agonist) [45]. An additional question assessing forced expiratory volume in 1 s (FEV_1_) (% predicted, pre-bronchodilator) is completed by the researcher. The ACQ contains 7 items rated on a 7-point scale (0 = without limitation, 6 = maximum limitation), with a higher score indicating worse control. The ACQ has been validated for Brazilian Portuguese [46]. Previous studies have demonstrated that scores lower than 0.75 points are associated with good asthma control, whereas scores greater than 1.5 points are indicative of poorly controlled asthma [44]. A change of at least 0.5 points on the ACQ is regarded as clinically significant [47].

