### Data analysis

#### Sample size

Sample size was calculated based on the minimal important difference of 0.5 points between the groups [47] on the ACQ questionnaire, with a standard deviation of 0.72 [73]. A sample size of 55 patients will be sufficient to detect an effect size of 0.5 between the 2 arms for 80 % alpha 2-sided, assuming up to a 20 % loss to follow-up.

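### The ANOVA named for the primary outcome uses only patients with a final ACQ, and the article gives no rule that brings the others into the promised intention-to-treat analysis

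*Protocol article*

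**What the plan says.** All references are to the protocol article.

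- **Statistical analysis**, principle: "An intention-to-threat analysis will be used to preserve the effects of group allocation and provide an assessment of the practical impact of the treatment". The word is a misprint for intention-to-treat.
- **Statistical analysis**, method: "Comparisons of the initial and final data will be analyzed via a two-way repeated-measures analysis of variance".
- **Primary outcome**: "the absolute change in the asthma control questionnaire (ACQ) post intervention between the groups".
- **Experimental design**, timing: "The patients will be assessed before and after the interventions on 3 non-consecutive days". No intermediate ACQ is described.
- **Experimental design**, final visit: "All patients will complete 24 treatment sessions, after which they will be reevaluated". The legend of Fig. 1 likewise places the second evaluation after the 24 sessions. Neither place says what happens to a patient who stops earlier.
- **Sample size**: 55 patients, "assuming up to a 20 % loss to follow-up".

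The article does not say how a randomised patient without a final ACQ is handled. It also does not say that such patients are excluded.

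**The concern.** The article commits to a principle and to a test. The principle is that everyone counts in the arm to which they were randomised. The test needs a before and an after value from each patient. The plan itself expects some patients to have no after value. Run as written, the test drops them without any stated decision to do so.

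Randomisation protects the comparison of all patients allocated, not the comparison of those who return for the last visit. If patients who do badly are less likely to return, and this happens more in one arm, the difference in ACQ change is distorted. Heavier loss of poorly controlled patients from the exercise arm would flatter exercise. Heavier loss from the sham arm would hide a benefit.

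**Working it through.** **Inputs from the article.** N = 55, loss allowance 20 % and target difference 0.5 ACQ points (Sample size). One ACQ before and one after (Experimental design). Repeated-measures ANOVA (Statistical analysis). The two factors are read as group and time, which the article does not spell out.

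**Assumptions.** Deficit among dropouts D = 0.5 to 1.0 ACQ points. Between-arm difference in loss 10 to 20 percentage points. The article gives neither.

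**Step 1: the planned loss.** 55 × 0.20 = 11 patients without a final value, and 55 − 11 = 44 with one. Whether 55 follows from its own inputs is a separate matter and is not used here.

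**Step 2: what the test uses.** With two time points the patient effect cancels in d = final − initial. The group-by-time F equals t², where

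t = (mean d in exercise − mean d in sham) / (s_d × √(1/n_E + 1/n_S)).

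A patient without a final value has no d. That patient's single baseline value is absorbed by the patient's own effect.

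**Step 3: numerical check.** A data set of 55 patients was simulated, with 11 final values removed at random.

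| Model | Patients in the data | Group-by-time estimate | SE |
|---|---|---|---|
| ANOVA with patient effects | 55, of whom 11 baseline only | −0.5024 | 0.1671 |
| ANOVA with patient effects | 44 with both values | −0.5024 | 0.1671 |
| Mixed model, separate baseline means | 55, of whom 11 baseline only | −0.4998 | 0.1622 |

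Both ANOVA fits have 42 residual degrees of freedom (44 − 2). The 11 patients add nothing to the ANOVA. The mixed model uses their baselines, but the estimate hardly moves. Because the values were removed at random, this shows who contributes to each model and not how much bias either removes.

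**Step 4: size of a possible bias.** Let dropouts in each arm have a mean change worse than that of patients with both values by D, and let the proportions lost be p_E and p_S. The mean of all randomised patients in an arm is then worse by p × D than the mean of those with both values. The benefit of exercise is overstated by

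bias = D × (p_E − p_S).

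| D | Equal loss | 10-point difference (e.g. 25 % vs 15 %) | 20-point difference (e.g. 30 % vs 10 %) |
|---|---|---|---|
| 0.5 | 0 | 0.05 | 0.10 |
| 1.0 | 0 | 0.10 | 0.20 |

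Both example splits average 20 % with equal arms. Against the 0.5-point target the non-zero entries run from 0.05/0.5 = 10 % to 0.20/0.5 = 40 %. If loss is heavier in the sham arm, the sign reverses.

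**Step 5: where the zero depends on a common D.** Suppose instead that sham dropouts resemble the other sham patients, while exercise dropouts keep no extra benefit. An effect of 0.5 among patients with both values is then (1 − p_E) × 0.5 among all randomised: 0.45, 0.40, 0.35 or 0.30 for 10, 20, 30 or 40 % loss in the exercise arm. This too is an assumption.

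**The case against.** The strongest reply is that the article is merely silent on missing data. Imputation rules and analysis sets are commonly left to a full protocol or analysis plan, and neither is shown. Imputing the missing finals and then running the planned ANOVA would keep every randomised patient, so the principle and the method can be reconciled. This stands against any claim that the two cannot both hold. It does not remove the point: the article names a specific test, and that test run as described does not deliver the stated principle for patients without a final ACQ.

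A reader might also infer that the trial has chosen a completers' analysis and will exclude 11 patients. The documents do not support that. No section says such patients are excluded, and 20 % is a planning allowance. A patient who leaves the exercise sessions but attends the final assessment is analysed as allocated, so stopping treatment and lacking an outcome are different things. Even so, the article ties reassessment to the 24 sessions and gives no rule for early stoppers.

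The bias figures are also open to challenge. They rest on assumed differential loss, and the design works against it: the sham sessions match the exercise schedule and are meant to even out visits and attention. That is why the equal-loss case is shown.

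Finally, a mixed model on two ACQ values changes little and relies on data missing at random. This is right, and it is why the fix does not stop at the mixed model.

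**Conclusion.** The point holds in limited form. As written, the primary group-by-time comparison uses only patients with a final ACQ, so the named method does not by itself provide the intention-to-treat analysis that the article promises. At the planning allowance this concerns about 11 of 55 patients.

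A material bias is possible but not shown. It is zero with equal loss and a common deficit, and 0.05 to 0.20 ACQ points under the assumed deficits and loss differences. The article contains nothing that would place the trial within that range. The finding about which patients contribute depends only on there being two time points and no imputation or likelihood-based model. A full protocol or analysis plan that supplies one would settle it.

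**What to change.** 1. Make the primary analysis one that includes all randomised patients. Either fit a linear mixed model to initial and final ACQ with a common baseline mean and a group effect at the final visit, or use multiple imputation by arm (baseline ACQ, BMI, FEV1, sessions attended) followed by ANCOVA on final ACQ.
2. State that the final ACQ is sought from every randomised patient, whatever number of sessions was attended.
3. Add one sensitivity analysis for data missing not at random, for example with missing exercise-arm outcomes imputed from the sham arm. The mixed model alone cannot address this.
4. Report the ANOVA on patients with both values as secondary.

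The variables are already collected: BMI and FEV1 are among the planned measurements, and the session-by-session safety checks in both arms should make attendance known. The cost is some wording, a little more analysis work, the effort of recalling patients who stopped early, and software that fits these models if the named package (SigmaStat 3.5) does not.

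### The planned repeated-measures ANOVA tests the ACQ change without baseline adjustment; ANCOVA on the same data would be more precise at almost no cost

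*Protocol article*

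**What the plan says.** - **Endpoint** (Primary outcome): "The primary outcome of this study will be the absolute change in the asthma control questionnaire (ACQ) post intervention between the groups".
- **Timing** (Experimental design): "The patients will be assessed before and after the interventions on 3 non-consecutive days". Each patient therefore has one baseline and one final ACQ.
- **Method** (Statistical analysis): "Comparisons of the initial and final data will be analyzed via a two-way repeated-measures analysis of variance". This is the only method named for comparing continuous outcomes, so it covers the ACQ. The section mentions neither a baseline covariate nor which ANOVA term carries the treatment comparison. On significance it says "P values ≤ 0.05 will be considered statistically significant".
- **Planning figures** (Sample size): "Sample size was calculated based on the minimal important difference of 0.5 points between the groups", "with a standard deviation of 0.72", "80 % alpha 2-sided" (the 80 % can only sensibly be the power) and "assuming up to a 20 % loss to follow-up", for 55 patients in total. The section does not say whether 0.72 is the SD of the ACQ score or of its change.

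**The concern.** A two-way repeated-measures ANOVA gives three tests: group, time and group-by-time. Only group-by-time compares the change between arms. The time effect contains the education and weight-loss programme that both arms receive, and the group effect averages baseline with final values.

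With two time points, the group-by-time test is the t-test on change scores. That test in effect fixes the coefficient of baseline at 1. ANCOVA estimates the coefficient from the data, so it is more precise whenever baseline and final values are less than perfectly correlated, and it corrects for chance differences in baseline ACQ between two small arms. At stake is precision on the primary comparison, in a trial with about 22 to 27 patients per arm and with the baseline measurement already planned.

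**Working it through.** **Inputs from the article.** Difference 0.5; SD 0.72; two-sided alpha 0.05; 55 patients; loss up to 20 %.

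**Assumptions.** 1:1 allocation (no ratio is given); the full 20 % loss, so 55 × 0.8 = 44, or 22 per arm; equal SDs at both times and in both arms; r from 0.3 to 0.8.

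**The plan's own figure.** By the normal approximation, these inputs with 80 % power need 33 per arm, 66 in total, or 66/0.8 = 83 with loss. The stated 55 is not reproduced. That is a separate point; it is mentioned only because it fixes the number of patients used below.

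**Step 1: what the planned test is.** In a simulated two-arm data set with 22 per arm, the group-by-time F and the squared t on change scores were both 5.644. The two tests are the same.

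**Step 2: variances.** With s the SD of the score:
- change score: 2s²(1−r)
- ANCOVA: s²(1−r²)
- ratio: (1−r²) / [2(1−r)] = (1+r)/2

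**Step 3: power.** Noncentral t, 22 per arm, noncentrality 0.5 / (SD × √(2/22)).

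Reading A, 0.72 is the SD of change. The planned test has SD 0.72 at every r, so its standard error is 0.72 × √(2/22) = 0.217. The ANCOVA SD is 0.72 × √[(1+r)/2].

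Reading B, 0.72 is the SD of the score. The planned SD is 0.72 × √[2(1−r)] and the ANCOVA SD is 0.72 × √(1−r²).

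| r | Variance ratio | A: planned | A: ANCOVA | B: planned | B: ANCOVA |
|---|---|---|---|---|---|
| 0.3 | 0.65 | 61 % | 80 % | 48 % | 65 % |
| 0.5 | 0.75 | 61 % | 74 % | 61 % | 74 % |
| 0.6 | 0.80 | 61 % | 71 % | 71 % | 80 % |
| 0.7 | 0.85 | 61 % | 68 % | 83 % | 88 % |
| 0.8 | 0.90 | 61 % | 66 % | 94 % | 96 % |

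The gain runs from about 2 to about 18 percentage points. Using 41 instead of 42 error degrees of freedom changes power by less than 0.1 point. Estimating the baseline slope in 44 patients also inflates the ANCOVA variance by about 1/(44−4) = 2.5 % on average, which takes about one point at most off the ANCOVA columns.

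**Step 4: the group main effect, for comparison.** The arms are expected to be equal at baseline, so averaging the two times halves 0.5 to 0.25. Under reading B the SD of the average is 0.72 × √[(1+r)/2], which is 0.644 at r = 0.6. Power is then about 24 %.

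**The case against.** The strongest reply is that the plan contains no error here. The endpoint is change between groups, the group-by-time term tests exactly that, and under randomisation the test is valid and unbiased. Choosing ANCOVA is then a matter of efficiency, and where r is high and 0.72 is the SD of the score, the planned test already has 83 % to 94 % power and little is gained. All of this stands. It limits the point to precision but does not remove it, because the method is one the article itself fixes and the better one needs no further data.

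A reader might infer more than the documents support:

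- *That the trial would be judged on the group main effect, with power near 24 %.* The article does not say so, and its endpoint points to the interaction. The figure applies only if that term were misread as the treatment effect. An article may leave the naming of the term to a fuller document.
- *That randomisation is unstratified.* The allocation section does not mention stratification, and silence does not establish its absence.
- *That the planned test is biased by regression to the mean.* Randomisation makes this equal in both arms in expectation. ANCOVA corrects for chance baseline imbalance only.
- *That power is 61 % as a matter of fact.* It is 61 % only if 0.72 is the SD of the quantity analysed (reading A, or reading B at r = 0.5), with the full 20 % loss and equal arms.

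**Conclusion.** The point holds as a weakness of efficiency. The named analysis amounts to an unadjusted change-score comparison, and adjustment for baseline ACQ would remove 10 % to 35 % of its variance for r from 0.8 to 0.3. The exact gain cannot be fixed from the article, which gives neither r nor the meaning of 0.72. Adjustment does not bring power to 80 % in every scenario, so it does not replace a correction of the sample-size calculation. The planned test would not invalidate the trial, but the change should be made because precision is gained across the whole range examined.

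**What to change.** Replace the sentence on the repeated-measures ANOVA with wording such as: *The primary analysis is the WL+E minus WL+S difference in final ACQ, with 95 % CI, from an ANCOVA adjusted for baseline ACQ, tested at the two-sided 5 % level.* This still serves the stated endpoint: with baseline in the model, analysing the final score or the change gives the same group difference. Analyse continuous secondary outcomes in the same way, each with its own baseline. It would help to add that within-arm changes are descriptive.

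The cost is a change of wording and one degree of freedom. No extra data, visits or patients are needed.

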**Fig. 1 Fig1:**
[figure not shown]
Study flow chart. After being included in the study, the patients will be evaluated during 3 non-consecutives visits. Each of the groups will receive the same education program and will participate in the same weight loss program* (composed of nutrition and psychological therapy); however, only one of the groups will participate in exercise training, as the remaining group will perform a sham intervention (breathing and stretching exercises). The groups will performed 24 intervention session, after which they will undergo a second evaluation utilizing the same tests as the baseline evaluation

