#### Levels of anxiety and depression

Symptoms of anxiety and depression will be evaluated using the Hospital Anxiety and Depression Scale (HADS) [52], which consists of 14 items divided into 2 subscales (7 for anxiety and 7 for depression). Each item is scored from 0 to 3, with a maximum score of 21 points for each subscale. A score greater than 9 in each subscale suggests a diagnosis of either anxiety and/or depression [53].

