#### Sleep disorders

The Berlin questionnaire will be used to estimate the risk (low to high) of obstructive sleep apnoea syndrome (OSA) [54]. The questionnaire consists of 10 items, divided into the following 3 domains: snoring and witnessed apnoeas (5 items), daytime sleepiness (4 items) and high blood pressure/obesity (1 item). Each category is classified as positive if the score is ≥ 2 points. Additionally, if the patients have at least 2 positive categories, they will be considered high risk for developing OSA. The Berlin questionnaire has been translated and validated for Portuguese [55]. The ActiSleep monitor (Pensacola, FL, USA) will be also used to objectively evaluate the sleep of patients. The participants will be instructed to use the monitor over a period of 7 consecutive nights on their non-dominant wrist. During this monitoring period, the participants will keep a sleep diary in which they will record the times at which they fall asleep, as well as when they awake each morning. We will analyze the following parameters: the total amount of sleep, sleep latency, the number and duration of awakenings and sleep efficiency [56].

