#### Airway inflammation

Airway inflammation will be quantified using the exhaled fraction of nitric oxide (FeNO), using a portable analyser (NIOX MINO®; Aerocrine AB, Solna, Sweden), in accordance with ATS/ERS guidelines [72]. The patients will be asked to exhale fully while seated before inhaling through a NIOX filter until they will reach their total lung capacity, and immediately will exhale at a constant flow rate of 50 ml/s using a visual feedback system. The average levels of at least 3 acceptable measurements will be used. The patients will be instructed to avoid eating foods containing nitrate and caffeine and to avoid smoking and exercise 24 h before testing, as well as to refrain from ingesting either food or water for at least 2 h before testing. NO collection will be performed by the same professional at the same time of day in order to avoid changes in patients’ circadian rhythms. A cut off point of 25 parts per billion (ppb) will be used to either confirm or exclude a diagnosis of eosinophilic airway inflammation [72].

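### Categorical outcomes measured before and after are given a plain chi-square test with no stated contrast and no use of pairing or baseline status

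*Protocol article*

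**What the plan says.** The Statistical analysis section covers the method for both kinds of outcome in one sentence: "Comparisons of the initial and final data will be analyzed via a two-way repeated-measures analysis of variance, and the categorical outcomes, via the" χ² test. It names no paired test and no baseline adjustment for categorical data, and it does not say which two sets of proportions the test compares.

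The design makes these data paired. Experimental design: "The patients will be assessed before and after the interventions on 3 non-consecutive days". The Fig. 1 legend says of the end of treatment that "they will undergo a second evaluation utilizing the same tests as the baseline evaluation".

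Three sections give classifications that could enter such a test:

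- **Sleep disorders** defines a low/high result from the Berlin questionnaire: "if the patients have at least 2 positive categories, they will be considered high risk for developing OSA".
- **Levels of anxiety and depression** gives a cut-off for reading the HADS: "A score greater than 9 in each subscale suggests a diagnosis of either anxiety and/or depression".
- **Airway inflammation** gives one for FeNO: "A cut off point of 25 parts per billion (ppb) will be used".

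Only the first is plainly a categorical outcome. The other two are scores or concentrations with an interpretive threshold.

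**The concern.** Continuous outcomes get a method that takes account of both group and repeated measurement. Categorical outcomes, measured on the same patients at the same two times, get a test that can do only one of two things. It can compare arms on final status and leave the baseline information unused. Or it can compare initial with final status and treat two values from one patient as if they came from two patients.

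The first is valid but can be inefficient in a trial of this size. The second has the wrong variance and, run within an arm, does not address whether exercise adds to the weight-loss programme. Because the contrast is not fixed, an analyst could also settle it after seeing the data. Sleep disorders are part of the trial's stated hypothesis (Background), so the choice is not trivial, although these outcomes are secondary.

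**Working it through.** **Inputs.** From Sample size: 55 patients and up to 20 % loss, so 55 × 0.8 = 44 completers. The allocation ratio is not stated; 1:1 is assumed, giving 22 per arm, which is the planned worst case. From Statistical analysis: significance at 0.05. The article gives no event rate, within-patient correlation or power for any categorical outcome, so there is no plan figure to reproduce. Rates and correlations below are assumptions. Pairs of binary values were simulated from a latent bivariate normal with correlation ρ; φ is the resulting correlation between the binary values.

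**Reading A: arms compared on final status.** Chi-square = (p₁ − p₂)² / [p̄(1 − p̄)·2/n], n = 22. The comparator is the Mantel-Haenszel test stratified by baseline status. Baseline is 60 % in both arms.

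No true difference (60 % versus 60 %): chi-square rejects in 4.6 % to 4.8 % of runs for ρ from 0 to 0.9. Its p-values are valid.

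True difference (60 % versus 25 %), power:

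| ρ | Chi-square | Baseline-stratified |
|---|---|---|
| 0 | 0.66 | 0.66 |
| 0.3 | 0.66 | 0.67 |
| 0.5 | 0.66 | 0.70 |
| 0.7 | 0.67 | 0.75 |
| 0.9 | 0.66 | 0.85 |

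The loss runs from nothing at ρ = 0, through 0.70 − 0.66 = 0.04 at ρ = 0.5, to 0.85 − 0.66 = 0.19 at ρ = 0.9.

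**Reading B: initial versus final within one arm.** With equal true proportions p, the variance of the paired difference is 2p(1 − p)(1 − φ)/n. The chi-square test uses 2p(1 − p)/n, which is too large when φ > 0. Its approximate true alpha is therefore 2[1 − Φ(1.96/√(1 − φ))]. At φ = 0.33: 1.96/√0.67 = 2.39, which gives 0.017.

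Simulation with n = 22: no change at 50 % for the type I error, and a fall from 50 % to 20 % for power. McNemar = (b − c)²/(b + c), where b and c are the two discordant counts.

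| ρ | φ | Chi-square true alpha | Chi-square power | McNemar power |
|---|---|---|---|---|
| 0 | 0 | 0.050 | 0.55 | 0.51 |
| 0.3 | 0.19 | 0.029 | 0.56 | 0.60 |
| 0.5 | 0.33 | 0.016 | 0.56 | 0.67 |
| 0.7 | 0.49 | 0.007 | 0.56 | 0.78 |
| 0.9 | 0.71 | 0.0004 | 0.56 | 0.92 |

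McNemar's own type I error in these runs is 0.034 to 0.050. The exact version is more conservative: its power is 0.53 at ρ = 0.5, 0.61 at 0.7 and 0.68 at 0.9, so it overtakes chi-square only above about ρ = 0.5.

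**Cell sizes.** An expected count below 5 with 22 per arm needs a pooled proportion under 5/22 = 23 % or over 77 %. In the scenario above the pooled proportion is (0.60 + 0.25)/2 = 0.425, and the smaller expected count is 22 × 0.425 = 9.35.

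**The case against.** The strongest reply is that the sentence need not mean a before/after chi-square at all. Grammatically, the initial-versus-final comparison is the subject for the analysis of variance, and the categorical outcomes are a second subject. The primary outcome and the sample size are both framed between groups, so a between-arm test on final status is at least as natural. On that reading no pairing is violated, and an unadjusted chi-square test is valid in a randomised trial. This stands, and it limits the point.

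A reader might infer more than the article supports:

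- **That the p-values are wrong outright.** This holds only for the before/after reading, and there the error is conservative under positive correlation. False positives become rarer, not more frequent.
- **That arms will be compared through two separate within-arm tests.** The article describes no such procedure.
- **That sparse cells are likely.** No rates are given, and the assumed ones do not produce them.
- **That HADS and FeNO will be dichotomised for analysis.** The cut-offs are given as aids to interpretation, and the Discussion speaks of a reduction in FeNO, which is a continuous change.

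It can also be said that a condensed article leaves model detail to an analysis plan. That covers rules for sparse data. It does not cover a test that the article itself names without its contrast. The gain from pairing is not universal either: at zero correlation McNemar has slightly less power than chi-square.

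**Conclusion.** The point holds in a limited form. The named test ignores information that the trial collects, and the article does not say what the test compares. Between arms, the result is valid but loses about 0 to 19 percentage points of power, depending on how strongly final status follows baseline status. Within an arm, the test does not suit paired data: its true alpha falls from about 0.03 to below 0.001 as the latent correlation rises from 0.3 to 0.9, and it leaves the between-arm question unanswered.

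These sizes rest on 22 completers per arm, 1:1 allocation, and assumed rates and correlations. The effect is confined to secondary or mechanistic classifications, with Berlin risk the only certain one. The ACQ analysis is not touched. This is an inexpensive improvement and a needed clarification, not a threat to the trial's main conclusion.

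**What to change.** Replace the categorical part of the Statistical analysis sentence with a statement along these lines:

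- Binary outcomes are compared between arms at the final visit, adjusted for the same variable's baseline status, by logistic regression or by a Mantel-Haenszel analysis stratified by baseline status. An effect estimate with 95 % CI is reported.
- Any initial-versus-final change within an arm is described with McNemar's test and carries no claim about the difference between arms.
- The outcomes to be analysed as binary are listed. Berlin risk is one; HADS and FeNO are listed only if a dichotomy is really intended.

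The cost is a change of wording made before the data are analysed. Baseline and final status are already collected, so no visit, measurement or patient is added. The authors should confirm that their software can run the chosen method.
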